### **6.4 Recruitment and selection of participants (including informed consent)**

Participants will be recruited via public advertisement, including posters/flyers displayed at the University of Sydney, diabetes centres, the research site and on social media. We will also reach out to individual endocrinologists, general practitioners and diabetes educators with information on the study and interested practitioners can opt to receive a pack of flyers and Participant Information Sheets (PIS) to distribute as desired. Individuals wishing to take part in the study will be required to make initial contact with the research team by calling or emailing [name] (contact details provided on advertising materials) and/or completing an online survey via REDCap (hyperlink and QR code displayed on advertising materials). The survey will involve multiple screening questions to determine whether or not interested individuals are eligible to participate in the study. Survey responses will be assessed in the order they are received by one investigator (JT) against the pre-specified inclusion/exclusion criteria. Participants will be asked to provide valid evidence to confirm their T1D diagnosis, the duration of their diabetes, and their recent HbA1c result (e.g., hospital discharge summary, specialist letter, pathology report). Ineligible participants will be excluded and provided the reason(s) for exclusion via email or phone. Potentially eligible participants will receive a phone call from JT to clarify responses, provide additional screening information (e.g., habitual dietary intake, completed confirmation of support letter from their nominated HCP) and if deemed eligible, schedule their first clinic visit. At this point, participants will also be asked to provide contact details of their usual GP so they can be informed of their patient's decision to be involved in the study (Attachment 53). The first 20 eligible volunteers will enter the study (Figure 1).

#### **6.4.1 Inclusion criteria**

- Adults aged 18-70 yrs
- Residing within Australia
- Previously diagnosed T1D (confirmed with specialist letter/correspondence, diabetes duration  $\geq 6$  months, using multiple daily injections of insulin and/or insulin pump)
- Suboptimal glycaemic control (HbA1c  $> 7.0\%$ )

- BMI 18.5-39.9 kg/m^2
- Habitual dietary intake contains >150 g/day of total carbohydrates (assessed by a 24-hour diet recall collected by study dietitian)
- Independent free-living, able to understand study requirements, speak and understand fluent English, and both physically and cognitively able to provide their informed consent
- Willing and able to self-monitor blood glucose levels using both finger-prick and/or continuous/flash blood glucose monitoring devices on a daily basis
- Willing and able to learn and utilise dietary carbohydrate and protein counting skills
- Willing and able to titrate insulin dosages according to their dietary carbohydrate (+/- protein) intake in consultation with a member of their usual diabetes care team
- Owns and can competently use an iOS or Android mobile device that is able to receive text messages/calls and download free mobile applications from the *App Store* or *Google Play*
- Has access to and can competently use a computer, mobile or tablet device with internet connection for uploading data onto REDCap and for Zoom conferencing
- Be willing to visit an Australian Clinical Labs collection centre (<https://www.clinicallabs.com.au/location/>) on four separate occasions throughout the study

#### 6.4.2 Exclusion criteria

- HbA1c ≤7.0%
- Underweight (BMI <18.5 kg/m^2) or class III obesity (BMI ≥40 kg/m^2)
- Habitual use of an automated insulin delivery system to control blood glucose levels
- Habitual adherence to a fixed insulin regimen such that they are not confident in titrating insulin dosages according to their dietary intake.
- Previously diagnosed hypo unawareness
- Non-English speaking or unable to understand English
- Previous medical diagnosis of cognitive impairment and/or mental illness (not including depression and anxiety)
- Using medication to manage depression and/or anxiety and medications have been increased within the last three months
- Current physical impairment or disability that limits individual capacity to communicate with researchers and/or use the mobile application *Easy Diet Diary* (e.g., blind/vision impaired/deaf/speech impaired)
- Habitual dietary intake contains ≤150 g/day of total carbohydrates
- Usual dietary intake strictly excludes animal-based protein (e.g., vegan diet)

- Undertaken major change(s) to their insulin delivery method and/or glucose monitoring method within the last three months, of which they are unfamiliar (e.g., switched from injections to insulin pump and has never used pump before, or from multiple daily finger pricks to CGM and has never used CGM before)
- Recent pregnancy or lactation (within the last six months)
- Planning to get pregnant within the next 12 months
- Self-identifies as current or recent smoker (within the last 6 months)
- Significant weight change ( $\pm$  10% body weight) within the last three months
- Previous weight loss surgery
- History of malignancy (other than non-melanoma)
- History of thalassemia or other haemoglobinopathy
- Pre-existing anaemia
- Recent blood transfusion (within the last three months)
- A known family history of premature heart disease, including having a first-degree male relative (i.e., father or brother) or a first degree female relative (i.e., mother or sister) who had a heart attack, stroke or was diagnosed with cardiovascular disease before the ages of 55 or 65, respectively
- Previously diagnosed familial hypercholesterolaemia
- Previously diagnosed gastrointestinal disease (including inflammatory bowel disease [IBD]; not including irritable bowel syndrome [IBS] or coeliac disease) unless condition is treated and stable (e.g., no change in medications within the last 3 month and asymptomatic)
- Previously diagnosed liver disease (including liver cirrhosis; not including fatty liver), chronic kidney disease (CKD; eGFR  $<60$ ), respiratory disease (not including stable treated asthma), thyroid disease (including goitre; not including stable treated hyper- or hypothyroidism) or cardiovascular disease (including coronary heart disease, heart failure, cardiomyopathy, congenital heart disease, peripheral vascular disease and stroke; not including hyperlipidaemia or hypertension)
- Previously diagnosed neurological disorder (including high-frequency episodic migraine [10-14 headache days per month], chronic migraine [ $\geq 15$  headache days per month], epilepsy, dementia, multiple sclerosis and Parkinson's disease; not including low frequency migraines [ $<10$  headache days per month])
- Previously diagnosed with a clinical eating disorder (including anorexia nervosa, bulimia nervosa or binge eating disorder) (within the last five years)

- Existing patient of [name] (Credentialled Diabetes Educator), [name] (Medical Doctor), [name] (Endocrinologist) or [name] (Accredited Practising Dietitian)

### 6.5 Control Period

The schedule of events is clearly outlined in Table 1 and Figure 1. During the first study visit (start of week 0), [name] will explain the health information that needs to be collected by the participants across the following seven days. This will involve wearing a continuous or flash blood glucose monitoring device and recording insulin dosages and food intake. Participants will be provided with the necessary devices and resources required to collect this information and instructed on how to use them (e.g., continuous blood glucose monitor, insulin logbook, online diet tracking App, kitchen scales). Participants will also be provided with a pre-paid pathology request form (from iMedical, <https://imedical.com.au>). The study dietitian will help the participants locate their nearest Australian Clinical Labs pathology collection centre and participants will be instructed on when to visit this centre (Figure 1). Participants will be provided with a resource ('Preparing for your blood test'; Attachment 49) to instruct them on safely preparing for their blood test. After seven days (end of week 0), participants will attend their local Australian Clinical Labs collection centre after an overnight fast (10-12 hours). Any participant who has needed to treat hypoglycaemia ( $<4.0$  mmol/L) within the fasting window of their blood test will be advised to contact [name] (study dietitian) and organise their blood test on another day (ideally, the following day). A trained pathologist will take a set of blood samples using standard procedures and the samples will be analysed by Australian Clinical Labs. Participants will be instructed to have a meal and drink fluids immediately ( $<30$  mins) after their blood has been drawn.

Further outcome data, including quality of life, diet satisfaction, BMI, waist circumference, resting blood pressure, and physical activity level will also be collected on the same day (or within a reasonable timeframe i.e.,  $\leq 3$  days). [name] will also obtain results from the continuous/flash blood glucose monitor, insulin logbook and online diet tracking App from participants at this time-point. Outcome measurements will be directly inputted into REDCap by [name].

After all baseline data (for the control period) has been collected, [name] will provide participants with instructions for the next four weeks which is to maintain usual patterns of eating, exercise and T1D management (Attachment 24). However, participants will be required to test their blood glucose levels at least six times daily, in accordance with standard

diabetes management practices, using whatever method(s) they usually use to test glucose. The dietitian will provide instructions and written resources on blood glucose monitoring (Attachment 47), managing hypoglycaemia (Attachment 48) and managing sick days (Attachment 46) (Table 1). There will be a diet session (Diet Session 0) scheduled in after two weeks and some basic diet education on carbohydrate counting (Attachment 25) and reading food labels (Attachment 26) will be provided (Table 1). During the last week of the control period, all of the same health assessments described above will be repeated (Table 1 and Figure 1). On the last day of the control period (end of Week 4), participants will have their first diet session of the intervention period (Diet Session 1) with the study dietitian and the intervention period will commence.

## 6.6 Intervention Period

### 6.6.1 LC diet

The dietary prescription is based on previously reported approaches shown to be safe and effective in multiple studies of LC diet interventions conducted in individuals with T2D [9].

This study will investigate a LC diet with an adaptive carbohydrate prescription that starts at 50 g of digestible carbohydrate per day and is then adapted (increased or decreased) within a broader range of 25-75 g/day according to individual blood glucose levels and personal preference. Participants will also be encouraged to distribute carbohydrates evenly across the day such that total carbohydrates do not exceed 20 grams at single eating occasion. To help participants reach nutritional adequacy, they will be encouraged to consume at least one serve of protein foods (150 g portion) with each main meal and to have three main meals daily, with or without snacks (participant preference). Participants will be given a food list with suggested food sources of proteins, fats, and carbohydrates to assist with meal structuring (Attachment 30). The intake of whole foods will be emphasised (e.g., vegetables, fruits, nuts, seeds, whole grains, meat, fish, eggs, yoghurt, milk, butter, unrefined fats and oils, etc.), while the intake of refined and highly processed food products (e.g., pastries, frozen meals, refined cereals, ice-cream, fruit juice, muesli bars, etc.) will be discouraged. Sample 3-day meal plans will also be provided to participants as a guide. There will be no upper limit intake restrictions on recommended sources of proteins and fats.

Recommendations for alcohol intake will be a maximum of two standard drinks daily with at least three alcohol-free days each week.

Individual dietary strategies will be geared toward helping participants meet the Recommended Daily Intake (RDI) and Adequate Intakes (AI) for essential nutrients including water (<https://www.nrv.gov.au/nutrients>), except for sodium wherein the estimated requirements for all participants are expected to increase as a result of lower insulin levels with adherence to the dietary intervention [20]. The adjusted recommendations for sodium in this intervention will be 3000-6000 mg/day for individuals with and without hypertension [21] to prevent sodium deficiency. Participants will be recommended to include at least 1.5 teaspoons of iodine-rich salt daily, as this will also help them meet their daily requirements for iodine. The recommended amount of salt will be provided to participants in pouches, and they will be instructed to measure out 1.5 teaspoons daily and add to foods and drinks.

Diet sessions will follow the structure outlined in Table 1. Participants will receive dietary instruction, strategies, and education, including written resources developed by the study dietitian (adapted from relevant NDSS facts sheets available from: <https://www.ndss.com.au/about-diabetes/resources/>). Dietary education will incorporate information on carbohydrates, proteins and fats, including carbohydrate and protein counting (given the need to take protein into account when calculating meal-time insulin requirements with habitual carbohydrate restriction <100 g/day [22]). Participants will be encouraged to use the *Easy Diet Diary* mobile application (Xyris software) throughout the study to assist with accurate carbohydrate and protein counting for calculating insulin requirements, and as a means of helping them achieve their carbohydrate prescription.

There will be opportunity to change the carbohydrate prescription after four and eight weeks. At these diet sessions, participants will discuss their dietary intake, blood glucose levels and individual preferences with the study dietitian. The study dietitian will provide an assessment based on their clinical judgement and together, the patient and dietitian will make a decision on whether or not to increase or decrease the carbohydrate prescription. In all cases, the adapted carbohydrate prescription will be specific (to the gram) and remain within the range of 20-75 g/day. E.g., 1: If a participant is struggling to adhere to a carbohydrate prescription of 50 g/day and is actually consuming 90 g/day, then the dietitian and participant might decide a prescription of 75 g/day is more achievable. E.g., 2: If a participant is closely adhering

to a 50 g/day but their blood glucose levels are still consistently above target after meals, then the dietitian and participant might decide a prescription of 30 g/day is required for better blood glucose control. This adaptive, patient-led approach is designed to take individual variations in dietary preferences and insulin sensitivity into account.

### **6.6.2 Insulin management & self-monitoring of blood glucose**

The purpose of this study is to investigate a LC dietary intervention. However, it is not possible to make major changes to the dietary management of T1D without considering the subsequent required change(s) to insulin management. As such, all participants and their nominated HCP will be provided with an information pack (developed by the study diabetes educator, dietitian, physician and endocrinologist) and adapted from relevant NDSS fact sheets available from: <https://www.ndss.com.au/about-diabetes/resources/> at the beginning of the intervention period that contains suggested guidelines for insulin management on a LC diet. The information pack includes resources relating to general considerations for insulin management on a LC diet; blood glucose self-monitoring; managing hypoglycaemia; and managing sick days. The information pack will be provided to participants by the study dietitian during Diet Session 1, and participants will get access to pre-recorded videos of the study diabetes educator explaining the resources. The information will also be discussed during a brief Telehealth session (~30 min) with the study diabetes educator, which will be scheduled within the first two weeks of the intervention period (Table 1, Figure 1). The purpose of this session with the study diabetes educator is to clarify the information contained in the resources, provide participants with an opportunity to ask questions about insulin management on a LC diet and to reduce the burden placed on participants' nominated HCP. This will be the only scheduled session with the study diabetes educator and all participants will be given regular reminders to follow up with their nominated HCP for all matters relating to insulin management, including individualised advice on insulin titrations. The study dietitian, diabetes educator, physician and endocrinologist will also be available throughout the duration of the study to provide support via Telehealth (phone or Zoom) to the participants' nominated HCPs, if needed.

Participants will be required to perform usual care practice self-monitoring blood glucose readings before each meal and two hours after meals (measured using their own blood glucose monitoring device) for insulin calculations and adjustments, and to

review their dietary carbohydrate prescriptions with the dietitian. Blood glucose targets will be consistent with standard practice diabetes targets and are:

- 4-8 mmol/L when fasting and before meals
- 4-10 mmol/L two hours after starting meals

Participants will be encouraged to share their glucose data with the study dietitian, either via their glucose monitoring software online or by downloading their glucose data from their glucose-monitoring device (which stores the blood glucose data) and providing it to the study dietitian via email or Zoom conferencing for discussion/review. This data will be used for monitoring purposes only and will not be used for the formal outcome analysis.

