### 7.3.2 Hypoglycaemia

Hypoglycaemia is a common acute complication of T1D which generally results from the difficulties in predicting expected rises in blood glucoses levels and accurately calculating insulin requirements. Due to the expected change(s) in insulin requirements as a result of the diet intervention, there is a risk of participants miscalculating their insulin requirements in the early stage of the intervention which could lead to increased frequency and/or severity of hypoglycemia. This will be mitigated by close monitoring of blood glucose levels, regular contact with the study dietitian, ongoing support from a nominated HCP, and oversight/supervision by the study physician, study diabetes educator and study endocrinologist.

Hypoglycaemia is defined by Diabetes Australia as a blood glucose level below 4 mmol/L [27]. The resources developed by the study dietitian and diabetes educator titled 'Managing hypoglycaemia' (Attachments 42 and 48) provide participants with information and guidelines on preventing and/or managing hypoglycaemia during the study. Participants will be required to test their blood glucose levels at least six times every day (i.e., before and 2 hours after each meal) using their own glucose monitoring

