device, as per standard of care diabetes practice. They will also be encouraged to test their blood glucose levels before going to bed and before driving or participating in exercise. Participants will also be advised to test their glucose more often if they are: feeling sick or stressed; more or less physically active; experiencing more hypos than usual; experiencing changes in their routine; experiencing night sweats or morning headaches; noticing frequent instances of high blood glucose levels; and/or starting on new medications. Participants will be asked to provide their blood glucose data from their blood glucose monitoring device to the dietitian for review every fortnight throughout the study. If using a CGM or flash glucose monitor (FGM), any reading(s)  $<4$  mmol/L should be confirmed with a finger prick device. If two or more readings across a 14-day period are  $<4.0$  mmol/L then the dietitian will flag the case with the study endocrinologist. The overseeing endocrinologist will then make a decision to either (a) continue until the next review (14 days); (b) refer them to their nominated HCP or GP for independent review; or (c) refer them to the study diabetes educator or study physician for review. If [name] is unavailable, then [name] will be consulted to review the case. All cases referred will be documented and used to assess safety of the intervention in the data analysis and reporting. Participants with hypo unawareness will be excluded from participating in the study. However, if any participant believes they might have developed hypo unawareness during the study, they will be advised to contact [name] (study dietitian) as soon as possible, who will flag the case with the study endocrinologist to be assessed on an individual basis.

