## 9. OUTCOMES

All primary, secondary and additional outcomes will be measured at three time-points: (1) pre-control period, (2) post-control period / pre-intervention period, and (3) post-intervention period. The only data being collected at follow up (12 weeks post-intervention) is HbA1c, total daily insulin (previous 24 hours), dietary intake (previous 24 hours), diabetes-related quality of life and diet satisfaction. Refer to Table 1 for a clear description of what outcomes are being measured at what time-points throughout the duration of the study for each participant. Refer to Figure 1 for an overview of this information.

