### 9.2 Secondary outcomes

- Glycaemic variability (GV) markers (including Standard Deviation (SD) intraday and mean amplitude of glycaemic excursions (MAGE) [derived from 7-day CGM/FGM data]
- Frequency of hypoglycaemia (<3.5 mmol/L with or without symptoms) [derived from 7-day CGM/FGM data]
- Total daily insulin (TDI) [the sum of all long-acting and rapid-acting insulin given over a 24-hour period derived from a 3-day self-report insulin log]
- Quality of life [measured using the 15-item DQOL Brief Clinical Inventory [25]]

GV markers have been identified as independent risk factors for diabetes complications including CVD, underscoring the importance of this assessment to more rigorously evaluate the effect(s) of the diet intervention on diabetes management.

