| Diet session 2
(during week 7)  | 
 
• Telehealth call (Zoom) with study dietitian.
 
• Review of dietary intake (collect diet history or review Easy Diet Diary tracking) and usual care blood glucose monitoring.
 
• Provide individualised dietary strategies for adhering to the intervention.
 
• Review understanding of information provided in diet session 1.
 
• Diet resources discussed in this session:               
 
- Dietary proteins
 
- Dietary fats
 
- Snack ideas
 
 
 
• Participants prompted to report any adverse events experienced (self-report) over previous 2 weeks (e.g., hypoglycaemia (<3.5 mmol/L), digestive issues, low energy levels, headaches, etc.)
 
• Participants encouraged to follow-up with their nominated healthcare professional to discuss insulin management.
 
                                                                                                                                                                                                                                                                                                                                          |

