| (during week 13)                                                                        | 
 
Review of dietary intake (collect diet history or review Easy Diet Diary tracking) and usual care blood glucose monitoring.
 
Discuss individual preferences, including any challenges or barriers to achieving the recommended carbohydrate target.
 
Carb target adjustment (opportunity 2): If appropriate, negotiate an adapted carbohydrate prescription (i.e., increase or decrease within 25-75 g/day) with the primary goal of achieving pre-specified blood glucose targets (4-6 mmol/L fasting, 4-8 mmol/L 2 hours post meal).
 
New meal plan provided, if applicable (25 g/day or 60 g/day sample meal plans).
 
Provide individualised dietary strategies for adhering to the intervention.
 
Review understanding of information provided in diet session 4.
 
Participants prompted to report any adverse events experienced (self-report) over previous 2 weeks (e.g., severe hypoglycaemia, digestive issues, low energy levels, headaches, etc.)
 
Participants encouraged to follow-up with their nominated healthcare professional to discuss insulin management.
 
      |

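### The hypoglycaemia outcome samples only the last week of the diet, early readings reach reporting only as referred cases under a different threshold, and the self-report prompt changes partway

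*Protocol*

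**What the plan says.** Section 4 hypothesises that the diet will reduce the frequency of hypoglycaemia. Section 9.2 defines the secondary outcome: "Frequency of hypoglycaemia (<3.5 mmol/L with or without symptoms) [derived from 7-day CGM/FGM data". Section 9 fixes when it is taken: "All primary, secondary and additional outcomes will be measured at three time-points", namely before the control period, after it, and after the intervention. Section 6.6.6 and clinic visits 5 and 6 in Table 1 place the last of these in week 16.

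Section 7.3.2 says of the diet change that "there is a risk of participants miscalculating their insulin requirements in the early stage of the intervention", and that this could raise the frequency or severity of hypoglycaemia.

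Participants also test with their own devices at least six times a day, and the dietitian reviews the data every fortnight. Section 6.6.2 says of the shared data: "This data will be used for monitoring purposes only and will not be used for the formal outcome analysis". Under Section 7.3.2, two or more readings below 4.0 mmol/L in 14 days are flagged to the study endocrinologist, who either lets the participant continue or refers them. The section then says: "All cases referred will be documented and used to assess safety of the intervention in the data analysis and reporting".

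Table 1 also sets a fortnightly self-report prompt. At Diet Session 2 it reads "Participants prompted to report any adverse events experienced (self-report) over previous 2 weeks (e.g., hypoglycaemia", with below 3.5 mmol/L in brackets. Sessions 3 and 4 use the same example. At Sessions 5 and 6 it reads "over previous 2 weeks (e.g., severe hypoglycaemia, digestive issues, low energy levels, headaches, etc", and the text shown does not define severe. Table 1 lists no such prompt at Diet Session 0.

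**The concern.** The protocol names a risk period and then measures its hypoglycaemia outcome as far from that period as the diet phase allows. If lows rise while insulin is being re-titrated and settle later, the planned comparison of week 16 with weeks 0 and 4 would show no change or an improvement. The report could then support the Section 4 hypothesis for the diet as a whole.

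The other sources do not supply a frequency for the missing weeks. The own-device readings are outside the outcome. The referral route counts cases at another threshold. The prompt covers the early weeks with a broad example and the late weeks with a narrower one, and has no control-period counterpart. Any bias from that change in wording would run towards an apparent fall.

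**Working it through.** The plan gives no figure on this point to reproduce. The check is a reading of the schedule, one fraction and an illustration.

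**Step 1: coverage of the formal outcome.** The synopsis gives a 12-week intervention, and 12 × 7 = 84 days. One 7-day wear falls within it (Table 1, clinic visit 5; Section 6.6.6).
- Covered: 7 / 84 = 8.3%, all at the end.
- Not covered: 77 / 84 = 91.7%, including the whole early stage.

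**Step 2: what exists for the diet weeks.**

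| Source | Diet weeks | Definition | Use |
|---|---|---|---|
| Study sensor (6.6.6, 9, 9.2) | 16 | below 3.5 mmol/L | Secondary outcome |
| Shared own-device data (6.6.2) | 5 to 16 | none set for analysis | Monitoring only |
| Referred cases (7.3.2) | 5 to 16 | flagged at two or more readings below 4.0 mmol/L in 14 days, then a decision | Safety reporting, as cases |
| Prompt, Sessions 2 to 4 (weeks 7, 9, 11) | previous 2 weeks | example: below 3.5 mmol/L | Self-report |
| Prompt, Sessions 5 and 6 (weeks 13, 16) | previous 2 weeks | example: severe, undefined | Self-report |
| Adverse events (8.1) | whole diet | needed health care and attributed to the study | Adverse-event form |

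Only the first row yields a frequency at the outcome's threshold, and it covers week 16 alone. The referral row counts people or reviews rather than episodes, and it is unclear whether a flagged participant who is allowed to continue counts as referred. The Section 8.1 definition leaves out lows that participants treat themselves.

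**Step 3: what this could hide.** The rates here are assumptions; the protocol gives none. Let the hypoglycaemia rate relative to control be *a* in the first 4 diet weeks and *b* in the other 8. The diet-period average is

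R = (4a + 8b) / 12,

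while the week-16 sensor shows *b*.

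| | b = 0.7 | b = 0.8 | b = 1.0 |
|---|---|---|---|
| a = 1.5 | 0.97 | 1.03 | 1.17 |
| a = 2 | 1.13 | 1.20 | 1.33 |
| a = 3 | 1.47 | 1.53 | 1.67 |

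For example, (4 × 1.5 + 8 × 0.8) / 12 = 12.4 / 12 = 1.03. R exceeds 1 when a > 3 − 2b. With b = 0.8, an early rate above 3 − 1.6 = 1.4 times control is enough to make the 12-week average worse than control while the outcome shows a 20% reduction. In eight of the nine cells the average is above 1 and the sensor shows 1 or less.

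**The case against.** The sensor outcome has a sound rationale. The same 7-day procedure is used at weeks 0, 4 and 16, so the within-participant comparison is like for like, and week 16 is a reasonable time to look for the established effect of the diet. The own-device data are weaker. Section 6.5 lets participants use their usual method, and Section 6.6.2 only encourages sharing. Section 7.3.2 advises more testing when lows are more frequent and asks that low sensor readings be confirmed by finger prick, so lows generate extra readings. Counting readings with the number of tests as an offset would not correct for that. All of this stands. It is a reason to keep these data out of the secondary outcome and not to test them formally. It is not a reason to leave the early weeks without any summary.

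Three stronger readings are tempting, and the documents do not support them.
- A reader might infer that the fortnightly data are barred from all analysis, or that Sections 6.6.2 and 7.3.2 contradict each other. Section 6.6.2 excludes them from the formal outcome analysis only. Section 7.3.2 carries referred cases into safety reporting, which is a separate use.
- A reader might infer that reported hypoglycaemia will fall at Sessions 5 and 6. The prompt asks about any adverse event and its examples are open-ended, so milder lows are not excluded. Reports could fall, but this is not certain.
- A reader might infer that the two-reading flag would catch nearly everyone and so carry no information. The protocol gives no rate of low readings, lows cluster, and it is referrals rather than flags that are reported.

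It could also be said that tabulation belongs in the analysis plan. That holds for layout. But the protocol itself excludes the readings and fixes the prompts, and no analysis plan can recover events that were asked about differently.

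**Conclusion.** The point holds in limited form. On the diet, the frequency of hypoglycaemia is measured on 7 of 84 days (8%), all in week 16, although the protocol names the early stage as the risk period. Weeks 5 to 15 reach reporting only as referred cases at 4.0 rather than 3.5 mmol/L, as health-care-requiring adverse events, or through a self-report prompt whose wording changes and which has no control-period counterpart. The coverage figure is exact. The size of any masked early rise is unknown, and the ratios above only show that a modest early excess would be enough. The primary outcome, HbA1c, is unaffected. The defect should be corrected because the correction is cheap and the alternative is a conclusion about reduced hypoglycaemia that is wider than the data behind it.

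**What to change.** 1. **Table 1.** Use one identical hypoglycaemia prompt, carrying the outcome's definition of below 3.5 mmol/L, at Diet Sessions 0 and 2 to 6. If severe events are also wanted, define the term and ask about them separately at every session.
2. **Section 6.6.2.** Replace the exclusion sentence with wording such as: *Fortnightly own-device data will not contribute to the sensor-based secondary outcome. They will be summarised descriptively as safety data: readings, or days with readings, below 3.5 and below 4.0 mmol/L per participant, for the control weeks, weeks 5 to 8 and weeks 9 to 16. Scheduled pre- and post-meal tests will be used where identifiable, finger-prick and CGM/flash users will be shown separately, and completeness will be reported.* Table 1 lists no glucose review at Diet Session 0, so it should state that the control-period download is collected.
3. **Reporting.** Limit any conclusion from the sensor outcome to the final diet week against the pre-diet weeks. Report flagged cases and referred cases separately, as description only, and state whether a flagged participant who continues counts as referred.

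The clinical flag rule is left as it is. The cost is some data cleaning, with data that will be incomplete and device-dependent, which is why no formal test and no offset model are proposed. No visits or tests are added.
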